### Eligibility criteria, recruitment, and consent

Patients are eligible for inclusion if they are ≥65 years of age, acutely admitted to the ED, community-dwelling, and residing in one of the following municipalities: Hvidovre, Copenhagen (Districts of West and South Western Copenhagen), or Brøndby. Exclusion criteria are inability to understand Danish, inability to cooperate physically (e.g., hearing or speech impairment), or cognitively (e.g., dementia or unconsciousness), isolation room stay, not Caucasian, and admission due to suicide attempt or terminal illness.

Participants are recruited up to 36 h after admission. Each morning (Monday through Thursday), patients are assessed for eligibility from a randomized computer-generated list of all patients in the ED. Eligible patients are informed about the trial both verbally and in writing by a team of seven researchers and are given the possibility of a reflection period of 24 h to consent to participation. Participants are given the option to consent separately to GFR measurement and pharmacogenetic test. After obtaining written informed consent, each participant is randomized to either the intervention group or standard care, and baseline data are collected. After baseline data are collected, each participant is informed about the result of the randomization by staff performing the intervention.

The following strategies are implemented to minimize the effect of staff shortages on patients recruitment: (1) on days with insufficient hospital staff available to perform the MULTI-NUT-MED intervention, only patients with a Mini Nutritional Assessment Short-Form (MNA-SF) [60] score >11 are recruited (to the MED intervention only); (2) on days with insufficient community-based staff available to perform future nutritional intervention (e.g., due to vacation or long term illness), patients from these municipalities are not assessed for eligibility; (3) if more than 35% of the first 50 included patients (*n* = 50) have an MNA-SF score >11, then the project leaders can decide to exclusively recruit patients with an MNA-SF score ≤11 2 days of each week in order to achieve a sufficient number of participants with an MNA-score ≤11 (see the “Sample size” section). The expected recruitment rate is two participants per week for 100 weeks.

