All municipalities offer food service (paid by the recipient) and home care meal support. None of the municipalities have systematic identification of malnutrition. The municipality of Hvidovre offers home visits from a dietician for citizens who experience unintentional weight loss or declining functional ability or if the municipality is informed of a citizen at risk of malnutrition during hospitalization. The dietician offers unlimited dietary counseling until the goal of counseling is reached, or the counseling is deemed to be unfruitful. The municipality of Copenhagen offers nutritional advice from a nurse to citizens identified as having malnutrition by care staff. The municipality of Brøndby offers dietary counseling from a community-based dietician to citizens with malnutrition who are identified by care staff. Due to the variation between the municipalities, randomization is stratified by the municipality.

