## Methods: assignment of interventions

### Allocation sequence generation

Participants are randomly allocated to either the intervention group or control group in blocks of 8 and stratified by age (<75 or ≥75 years of age), sex, and municipality. A random 1:1 sequence of two letters was generated for each block, with the statistical software R 3.6.0 (R Foundation for Statistical Computing, Vienna, Austria) using the sampling function. The randomization sequence was generated by a statistician uninvolved in the trial, and who was unaware of which letter was assigned to which group.

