### Statistical methods

#### Primary outcomes

Differences in MAI score, change from baseline to 8 weeks after discharge between the control group and pooled intervention group (MED and MULTI-NUT-MED intervention), will be evaluated by analysis of covariance (ANCOVA). The primary analysis will model the randomization group and baseline MAI-score as independent variables by the intention-to-treat principle. Additional analyses will be adjusted for potential confounders that are unequally distributed between groups despite randomization. Missing data on the primary end point will be accounted for by multiple imputations using the PROC MI procedure with fully conditional specification (FCS) and a minimum of 100 imputations. Imputation will use earlier measurements of the imputed outcome, number of medications, and randomization group, along with age and sex for prediction models.

Differences between mGFR and eGFR based on both the combination of creatinine and cystatin C will be evaluated by mixed linear regression analysis.

The difference in EuroQol-5D-5L score change from baseline to 16 weeks after discharge between the control group and MULTI-NUT-MED intervention group will be evaluated by ANCOVA. The primary analysis will model randomization group and baseline EuroQol-5D-5L as independent variables with either intention-to-treat analysis or per-protocol analysis, where participants are considered compliant if they received and were compliant to at least one intervention if one was recommended, two if two were recommended, two if three were recommended, three if four were recommended, and four if five or six were recommended. Additional analyses will be adjusted for potential confounders that are unequally distributed between groups despite randomization. Missing data on the primary endpoint will be accounted for by multiple imputations using the PROC MI procedure with fully conditional specification (FCS) and a minimum of 100 imputations. Imputation will use earlier measurements of the imputed outcome along with age, sex, and diagnosis codes for prediction models.

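### Both primary ANCOVAs omit the factors that stratify the randomisation, so precision may be lost and the MAI test may be mildly conservative

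*Protocol article*

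**What the plan says.** Under Allocation sequence generation, the Protocol article allocates patients "in blocks of 8 and stratified by age (<75 or ≥75 years of age), sex, and municipality", in a 1:1 ratio. The eligible municipalities are "Hvidovre, Copenhagen (Districts of West and South Western Copenhagen), or Brøndby". The Standard care section explains the third factor: "Due to the variation between the municipalities, randomization is stratified by the municipality". The variation it describes is in dietician, nurse and meal services.

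Under Statistical methods, Primary outcomes, both primary models are spelled out. For MAI: "The primary analysis will model the randomization group and baseline MAI-score as independent variables by the intention-to-treat principle". For the quality-of-life endpoint: "The primary analysis will model randomization group and baseline EuroQol-5D-5L as independent variables". No stratification factor is in either model. Any further adjustment is confined to secondary runs, described identically for both endpoints: "Additional analyses will be adjusted for potential confounders that are unequally distributed between groups despite randomization".

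The imputation models for both endpoints use age and sex as predictors. Municipality is in neither the imputation nor the analysis models.

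**The concern.** Stratified blocks push the two groups towards the same mix of age, sex and municipality. This removes some chance variation from the treatment difference. A model without those factors leaves their contribution in the residual and so counts it again in the standard error. If the factors predict outcome, the reported standard error is then larger than the true sampling variation. Intervals cover more than 95%, the test rejects a true null less than 5% of the time, and available precision is not used.

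The article names the independent variables of each primary model, so this is a stated choice and not a detail left to an unseen analysis plan. The choice also sits awkwardly with the rest of the article. Age and sex are treated as informative enough to impute the outcome, and municipality as important enough to stratify on, yet none of them enters the analysis.

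The additional analyses will probably not repair this. Stratification tends to balance these three factors, so a rule triggered by observed imbalance will rarely pick them. That rule selects covariates by chance difference and not by expected prognostic value.

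**Working it through.** **Inputs from the article.** Significance level 5% (taken as two-sided), power 80%, dropout 25%. MAI: difference 3, SD 5, N = 120. EuroQol: difference 0.15, SD 0.27, N = 130. Total enrolment 200. Age has 2 levels, sex 2 and municipality 3, giving 12 strata and 1 + 1 + 2 = 4 degrees of freedom as main effects.

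**Reproducing the plan's figure.** A two-sample t test for 3 points with SD 5 needs 45 per arm, 90 in total. 90 / 0.75 = 120, as stated.

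**Numbers analysed.** MAI with 200 enrolled: 200 × 0.75 = 150, or 75 per arm. EuroQol: 130 × 0.75 = 97.5, or 48.75 per arm.

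**Closed form.** Let R² be the share of outcome variance, left after the baseline score, that the strata explain. The article gives no value, so R² is an assumption, ranged from 0 to 0.10. The plan's SDs are taken as the residual SDs after baseline.

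- Interval width, adjusted over planned: f = √(1 − R²).
- True type I error of the planned model if the strata were perfectly balanced: 2 × (1 − Φ(1.96 / f)).
- Power with the strata added: Φ(δ / (SD × f × √(2 / n)) − 1.96), with n per arm.

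At R² = 0, the EuroQol calculation is 0.15 / (0.27 × √(2 / 48.75)) = 2.743, and Φ(2.743 − 1.96) = 78.3%. For MAI, 3 / (5 × √(2 / 75)) = 3.674, and Φ(3.674 − 1.96) = 95.7%.

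| Assumed R² | Width ratio f | Type I error of planned model, perfect balance | EuroQol power, 97.5 analysed | MAI power, 150 analysed |
|---|---|---|---|---|
| 0 | 1.00 | 5.0% | 78.3% | 95.7% |
| 0.02 | 0.99 | 4.8% | 79.1% | 96.0% |
| 0.05 | 0.975 | 4.4% | 80.3% | 96.5% |
| 0.10 | 0.949 | 3.9% | 82.4% | 97.2% |

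Perfect balance is too favourable. 200 / 12 is about 17 patients per stratum, roughly two blocks of 8, so many last blocks will be incomplete, and dropout disturbs balance further.

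**Simulation under the actual design.** Stratified blocks of 8 in 12 strata, 25% random dropout, and ANCOVA with and without the strata as main effects. Assumed shares: 60% aged 75 or over, 50% of each sex, municipalities 35/45/20%. There were 6,000 replicates for type I error and 3,000 for power. EuroQol was simulated as a random 70% subset of 185 enrolled, because nutritional status is not a stratification factor.

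| Endpoint | Assumed R² | Type I error, planned / adjusted | Width ratio | Power, planned / adjusted |
|---|---|---|---|---|
| MAI, 200 enrolled | 0 | 4.9% / 4.7% | 1.005 | 94.6% / 94.5% |
| MAI, 200 enrolled | 0.05 | 4.7% / 5.1% | 0.979 | 95.4% / 95.8% |
| MAI, 200 enrolled | 0.10 | 4.4% / 5.2% | 0.953 | 95.7% / 96.8% |
| EuroQol subset | 0 | 4.9% / 4.8% | 1.012 | 75.8% / 74.9% |
| EuroQol subset | 0.05 | 4.2% / 4.5% | 0.986 | 76.9% / 77.8% |
| EuroQol subset | 0.10 | 4.6% / 5.2% | 0.960 | 75.9% / 78.7% |

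Simulation error is about √(0.05 × 0.95 / 6000) = 0.3 points for type I error and √(0.77 × 0.23 / 3000) = 0.8 points for power. The direction agrees with the closed form. The EuroQol power gains are smaller: 0.9 and 2.8 points, against 2.0 and 4.1 in closed form.

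**The case against.** The primary models are valid as written. Their covariates are fixed in advance, the baseline score is included, and any error is on the safe side. Several stronger readings are tempting, and the documents do not support them.

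- A reader might infer that the primary analysis picks covariates after looking at imbalance. It does not: that rule applies only to the additional analyses, so the discretion it brings affects supporting results.
- A reader might infer inflated false positives or a biased estimate. Omitting balanced prognostic factors causes neither.
- A reader might treat conservatism as certain. It depends on an R² that the article does not give. At 0.02 the interval changes by 1%, and at 0 the adjusted interval is slightly wider.
- A reader might apply the gain from a starting power of 80% to MAI. The MAI calculation asks for 120 patients, but 200 are to be enrolled, so power is already about 96%.
- A reader might take the Standard care section as proof that municipality predicts MAI. It describes nutritional services and says nothing about prescribing. Even for EuroQol it describes care provision and not an association with outcome.
- A reader might want the MNA-SF category in the MAI model because it decides which intervention is given. It is not a randomisation factor, and both categories receive the same medication review, so its inclusion is optional.

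All of this stands and limits the size of the point. It does not remove the mismatch between how patients are randomised and how the two primary endpoints are analysed.

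**Conclusion.** The point holds as a modest one. Both primary ANCOVAs leave out the three stratification factors, and the planned additional analyses are unlikely to bring them in. For MAI, on the full randomised set, the consequence is intervals that are somewhat too wide and a mildly conservative test if the factors are prognostic. At an assumed R² of 0.05 to 0.10, simulated type I error was 4.7% to 4.4%, and adjustment narrowed the interval by about 2 to 5%.

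For EuroQol the case rests on precision more than on coverage, because balance on the strata is weaker in the malnutrition-risk subset. It matters more there because power starts at only about 78%. At the same R², adjustment narrows the interval by about 1 to 4% in simulation (2.5 to 5% in closed form). These sizes rest on the assumed R², on the plan's SDs standing for the residual SDs after baseline and, in the simulation, on the assumed stratum shares and random dropout.

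**What to change.** In both primary ANCOVAs, prespecify age (grouped as in the randomisation, or continuous), sex and municipality as covariates alongside the baseline score. Add municipality to both imputation models, which already use age and sex. In the additional analyses, replace selection by observed imbalance with a prognostic list fixed in advance. Adding the MNA-SF category to the MAI model is optional.

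The cost is about 4 degrees of freedom, which widens the interval by about 1% at most if the factors turn out not to be prognostic. No new data are needed, since the three factors are recorded for randomisation. It is more than an edit of wording, however. The trial began in October 2018 with about 100 weeks of recruitment expected, and the article appeared in September 2021. On that schedule recruitment was over, so the change to a published primary model should be a dated amendment made before unblinding.

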### Aims

The study involving acutely admitted older medical patients has three primary aims (1) to determine whether a medication review intervention is superior to standard care in improving medication appropriateness from admission to 8 weeks after discharge, (2) to determine the accuracy of eGFR equations based on various biomarkers compared to mGFR at a single-time point, and (3) to determine whether an individualized multimodal and transitional nutritional intervention is superior to standard care in improving the quality of life from admission and 16 weeks after discharge.

The study also has the following secondary aims which are related to the effect of the intervention: (1) to measure differences in polypharmacy, PIM use, and assessment of underutilization between the MED-intervention and standard care from admission to 8 weeks after discharge and (2) to measure of the differences in body weight, protein- and energy intake, mobility, cognition, frailty, the intestinal microbiome, and health care costs between the MULTI-NUT-MED intervention and standard care from admission to 8 and 16 weeks after discharge and 1 year after discharge (only health care costs).

Secondary aims, which are based on baseline data or data from the control group, include assessment of (1) how information from a broad pharmacogenetic test can potentially improve medication prescribing appropriateness; (2) how polypharmacy, PIMs, nutritional status, frailty, and inflammation modify the effect of the MED-intervention on prescribing appropriateness; (3) how non-GFR determinants affects eGFR and how the choice of eGFR equation affects medication prescribing; (4) how the choice of malnutrition classification criteria affects the prevalence of malnutrition; and (5) how different definitions of frailty affect the distribution of patients classified as frail or sub-frail as well as the responsiveness of these methods.

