### Sample size

The trial has three primary endpoints that build on mutually independent hypotheses [140]. Therefore, sample size calculations were performed for each endpoint as described below. All sample size calculations are performed for a significance level of 5%, power of 80%, and a dropout rate of 25%. Ethical approval was obtained for the inclusion of 200 participants in total to ensure enough power for all primary endpoints.
1: Based on a *t* test, a sample size of 120 is required to detect a clinical difference of 3 points (SD=5 points [36]) in MAI score change from baseline to 8 weeks after discharge between the control group and pooled intervention group (MED and MULTI-NUT-MED intervention).2: Based on a paired *t* test, a sample size of 62 participants is required to detect a clinically relevant difference of 4.0 mL/min/1.73m^2^ (SD=15, a R=0.73 [141]) between mGFR and eGFR based on the combination of creatinine and cystatin C. GFR is measured at baseline for all trial participants regardless of group allocation.3: Based on a *t* test, a sample size of 130 participants with or at risk of malnutrition is required to detect a clinically relevant difference of 0.15 points [142] (SD=0.27 [143]) in EuroQol-5D-5L score change from baseline to 16 weeks after discharge between the control group and MULTI-NUT-MED intervention group, assuming equal allocation in the two groups.

Given that patients are included independently of nutrition status and approximately 70% of patients are expected to have or be at risk of malnutrition [4], a total of 185 participants is required to achieve a sample size of 130 participants with or at risk of malnutrition.

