All additional confirmative outcomes will be evaluated by *t* test, Kruskal-Wallis test, chi-square test, two proportions *z* test, or Friedman’s analysis of variance depending on the distribution of the relevant variable. The analysis will be adjusted for multiple testing. Associations between variables will be evaluated by adjusted multiple regression models, and repeated measurements will be evaluated by mixed models of paired *t* tests or Fisher’s exact test. Missing data on secondary endpoints will be accounted for with multiple imputations as previously described.

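### The predictor list for imputing 8-week MAI omits four of the five effect modifiers to be studied, so interactions estimated on data imputed this way would shrink by roughly the missing fraction

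*Protocol article*

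**What the plan says.** - **Imputation model.** Under Statistical methods, Primary outcomes, missing 8-week MAI is handled by "multiple imputations using the PROC MI procedure with fully conditional specification (FCS) and a minimum of 100 imputations". The predictors are then named: "Imputation will use earlier measurements of the imputed outcome, number of medications, and randomization group, along with age and sex for prediction models".
- **Effect-modification aim.** The Aims section includes the question "how polypharmacy, PIMs, nutritional status, frailty, and inflammation modify the effect of the MED-intervention on prescribing appropriateness". The list it belongs to opens with "Secondary aims, which are based on baseline data or data from the control group, include assessment of".
- **Other analyses.** The Secondary outcomes section says "Missing data on secondary endpoints will be accounted for with multiple imputations as previously described". It describes no model, dataset or missing-data rule specific to effect modification.
- **Missing data.** The only rate given is the planning allowance in Sample size: "All sample size calculations are performed for a significance level of 5%, power of 80%, and a dropout rate of 25" per cent.

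**The concern.** An imputation model should contain every term that the later analysis estimates. The listed model has one group effect common to all patients. It therefore assigns each imputed patient the same expected treatment effect, whether well nourished or malnourished, frail or robust, inflamed or not. An analysis that then looks for differences in effect between these patients finds none among the imputed ones.

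Four of the five modifiers are absent from the list. The fifth, polypharmacy, is represented by number of medications, but no product with group is named.

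What is at stake is a secondary aim. It matters here because nutritional status decides whether an intervention patient receives the medication review alone or the wider nutritional programme, and the MAI analysis pools the two.

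**Working it through.** **Inputs.** From Sample size: MAI difference 3, SD 5, 5% significance (taken as two-sided), 80% power, 25% dropout, and about 70% expected with or at risk of malnutrition. From the Abstract: 130 of 200 patients with or at risk of malnutrition, which is 65%. Allocation is 1:1. Assumed, because the article gives no figure: true interactions of 3 and 5 MAI points.

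**Step 1, the plan's own figure.** The normal formula gives n per arm = 2 × 5² × (1.96 + 0.842)² / 3² = 43.6, so 44. The t test gives 44.6, so 45. Then 2 × 45 / (1 − 0.25) = 120, as stated. SD 5 and 25% are thus the values on which the MAI endpoint is sized.

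**Step 2, expected shrinkage.** Let δ be the true interaction and m the fraction with missing 8-week MAI, missing completely at random. Observed patients contribute δ and imputed patients contribute 0:

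expected interaction = (1 − m) × δ + m × 0 = (1 − m)δ.

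At m = 0.25 this is 0.75δ. At m = 0.10 it is 0.90δ.

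**Step 3, simulation.** The settings were 1:1 arms, SD 5, a binary modifier at 70%, a true interaction of 3 points, 1,500 replicates and 20 imputations. N was 400 for precision, unless stated.

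| Imputation model | Missing | Share of true interaction kept |
|---|---|---|
| As listed | 10% | 0.92 |
| As listed | 15% | 0.86 |
| As listed | 25% | 0.74 (0.76 at N = 200) |
| As listed | 35% | 0.66 |
| As listed, polypharmacy as modifier | 25% | 0.74 |
| As listed, PIM indicator correlated with baseline MAI | 25% | 0.74 |
| Modifier added as main effect only | 25% | 0.74 |
| Listed predictors, run by arm: nutritional status | 25% | 0.75 to 0.76 |
| Listed predictors, run by arm: PIMs | 25% | 0.77 |
| Listed predictors, run by arm: polypharmacy | 25% | 0.89 |
| Modifier and its product with group added | 25% | 1.01 (0.99 at N = 200) |

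**Step 4, dropout that depends on the modifier.** Let m1 and m0 be the missing fractions with and without the modifier, p its prevalence, and w = p(1 − m1) / [p(1 − m1) + (1 − p)(1 − m0)]. The share lost is m1(1 − w) + m0·w.
- m1 = 0.30, m0 = 0.133: w = 0.490 / 0.750 = 0.653. Loss = 0.30 × 0.347 + 0.133 × 0.653 = 0.19. Simulated: 0.19.
- m1 = 0.20, m0 = 0.367: w = 0.560 / 0.750 = 0.747. Loss = 0.20 × 0.253 + 0.367 × 0.747 = 0.32. Simulated: 0.31.

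**Step 5, effect on power.** With 200 patients, 150 observed and a modifier at 65%, the standard error of the interaction on observed data is √[4 × 25 / (150 × 0.65 × 0.35)] = √2.93 = 1.71. Power is Φ(3/1.71 − 1.96) = 0.42 for 3 points and Φ(5/1.71 − 1.96) = 0.83 for 5 points. Simulation of this setting (800 trials, 20 imputations) gave:

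| Approach | True 3: mean, power | True 5: mean, power |
|---|---|---|
| As listed | 2.28, 19% | 3.72, 58% |
| Modifier and product added | 3.00, 41% | 5.02, 84% |
| Observed data only | 2.98, 41% | 5.03, 83% |

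A further run, with missingness depending on age, gave 2.22 and 3.71 as listed. Imputing by arm with the modifier added gave 2.99 and 4.95.

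**Step 6, the primary comparison.** Under the listed model with data missing completely at random, the simulated overall group effect was −2.98 to −3.01 at the four missing fractions, against a true −3. In the two settings of Step 4 it was −2.87 and −3.12, a shift of about 0.13 points or less.

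**The case against.** The arithmetic is not in dispute. The question is whether the plan applies this model to this analysis.

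- **The link is inferred.** The predictor list is given for the primary endpoint, where it serves its purpose. The carry-over sentence refers to secondary endpoints, whereas 8-week MAI is a primary endpoint and effect modification is an aim. The article also gives a different predictor list for EuroQol-5D-5L, so the carry-over may mean the method and not this list. This stands, and the point has to be conditional.
- **The lead-in to the aim points elsewhere.** Taken literally, the aim would use baseline or control-group data and no comparison of arms. But such data cannot estimate how a treatment effect is modified. The wording does not remove the problem and needs correcting itself.
- **The list may not be exhaustive.** The text does not say that only these variables are used, nor rule out imputation by arm. However, it names group as a predictor, and by-arm imputation with the listed variables would help appreciably only for polypharmacy.
- **25% is a planning allowance.** MAI draws on chart data and the Shared Medication Card, so it may be missing less often than visit-based measures. This stands, and the loss scales with actual missingness.

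A reader might infer that the trial would wrongly declare the review equally effective in all subgroups. That does not follow. Attenuation is not a null finding, and the 3-point interaction assumed here, as large as the main effect the trial is sized for, has only about 41% power even when handled correctly. A non-significant interaction would be weak evidence either way.

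**Conclusion.** The point holds in conditional form. If the effect-modification aim is analysed on MAI imputed from the listed predictors, each interaction that the imputation model does not carry shrinks by roughly the fraction of missing 8-week MAI. That is about a quarter at 25% missing (19 to 31% in the simulations where dropout depends on the modifier), and 8 to 10% at 10% missing. If imputation is run by arm, the polypharmacy loss is about 11%. For this aim, the listed imputation then does worse than analysing observed patients only.

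The result rests on a common group effect in the imputation model and, for the simple factor, on data missing completely at random. The power figures rest on the assumed interactions, SD 5 and a binary modifier.

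It would go too far to say that a quarter of every interaction will be lost, or that the primary MAI result is compromised. The article does not commit this aim to imputed data, and the overall group effect is not materially affected. This is an inexpensive improvement to a secondary aim for which the trial was not sized.

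**What to change.** State which data the effect-modification analyses use, and choose one of these:

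1. Impute 8-week MAI separately within each arm, adding baseline MNA-SF, a frailty score, an inflammation marker (C-reactive protein or suPAR) and PIM count to the listed predictors. Equivalently, keep one model and add these variables, and number of medications, with their products with group.
2. Fit the interaction models on observed MAI, with the modifiers in the model.

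Adding the modifiers as main effects only, or imputing by arm without adding them, is not enough.

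Also reword the lead-in in the Aims section so that this aim is not placed among those using only baseline or control-group data.

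The cost is some plan wording and a few lines of code. Table 2 already schedules MNA-SF, frailty and the blood markers at baseline, and PIM count can be derived from the baseline medication list. The drawback of the first option is a few more imputation parameters for about 100 patients per arm.
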